### Study centres and participants

This study will be conducted at the ER of four Dutch hospitals: the AMC Amsterdam, Flevoziekenhuis Almere, Slotervaart Medical Center Amsterdam, VUmc Amsterdam. All subsequent patients that present themselves at the ER of one of the participating hospitals after an initial lateral ankle sprain will be treated according to standard protocol, including anamnesis, physical examination and (in case of positive Ottawa Ankle Rules (OAR)*) a radiograph [24]. When a mortise view and lateral radiograph is made and negative for ankle fractures or other joint pathology, patients are screened for eligibility according to the in -and exclusion criteria (Table 1).

**Table 1 Tab1:** Inclusion- and exclusion criteria

Inclusion criteria	Exclusion criteria
At least 16 years old	Present fracture or other joint pathology/bone matrix pathology
Visited the ER within one week after a lateral ankle sprain	A diagnosed OCD after primary inclusion
Agreed with being approached for this study	Medial ankle instability
Reported anterolateral ankle pain after an ankle sprain or ankle distortion	Previous ankle surgery
Filled out the baseline, 3-, or 6 month questionnaire; and the 12 month follow-up	An unreliable radiograph due to the angle in which it is made or low quality
	Acute surgical repair or the ATFL/CFL or any other form of surgery within 12 months after the ER visit

*Abbreviations*: *ER* Emergency Department, *AP* anteroposterior, *OCD* osteochondral defect, *ATFL* anterior talofibular ligament, *CFL* calcaneofibular ligament

*The OAR are a requirement at the ER according to Dutch protocols to conclude whether there is an indication for a radiograph. However, in cases of severe LAS patients there is a high risk at false positive OAR despite the absence of a fracture (due to a painful lateral malleolus with or without the ability to bear weight).

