### Definition CAI

Chronic ankle instability is defined as: *The perception of ‘giving-way’, in combination with a history of recurrent ankle sprains, the sensation of ankle instability and persistent disabilisty (pain, swelling* etc.*) that has not resolved in the time-frame from the first initial sprain up to the 12-months follow-up* [3, 25, 26]*.*

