#### Follow-up

A legally required waiting period of two weeks is observed prior to asking consent and sending the questionnaires to the patient’s home address or email address. Patients are asked to fill out the first questionnaire immediately which gives a T0 (baseline measure at approximately two weeks after the initial sprain). The subsequent evaluation time points are T1 interim evaluation after three months, T2 after six months, and T3 at twelve months. The questionnaires contain questions about patient characteristics, previous ankle sprains, treatment, restrictions and complaints. Additionally the questionnaires contains the Foot and Ankle Outcome Score (FAOS) and the Cumberland Ankle Instability Tool (CAIT) to evaluate recovery. To ensure all patients with CAI are identified, one year after their ER visit they will be contacted, inquiring on persisting complaints and ankle instability. Patients that indicate on the first questionnaire they sustained ankle sprains prior to their ER visit will not receive further follow-up questionnaires, as these patients are considered to have CAI and therefore need no extra monitoring to identify whether they develop CAI or not. They will not be included in the primary analysis as this may lead to overfitting of the current model. Concomitant neuromuscular adaptations and additionally may follow a different rehabilitation route due to familiarity with the complaints.

In case of persisting complaints six months after the ER visit, patients will be eligible for surgical treatment according to Dutch standards. This is to avoid unnecessary invasive treatment on patients as a large proportion recover by means of conservative treatment [7].

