#### PREDICT sample size

For a prognostic model at least 20 EPV is needed to optimize reliability and to avoid bias in regression coefficients [37–39]. Based on having maximally 16 variables with a minimum of 20 events per variable, a prevalence of 30–40% after an initial sprain, including a 10% loss-to-follow-up, a sample size of 1185 patients is needed to perform the internal and 1185 patients is needed to perform the external model validation, resulting in a total of 2370 patients (Table 2).

During the study the required sample size may change and will be recalculated accordingly in case one of the following scenarios occur:In case one or more radiographic factors have a low inter- or intra-observer reliability (ICC ≤0.70), they will be excluded from the risk assessment model and the sample size will be recalculated using the new number of prognostic factors. If radiographic assessments cannot be performed in more than 2 cases (> 5%) a candidate predictor will be excluded, as the problem is likely to recur and therefore cannot be adequately assessed, now and during future assessment (e.g. up to 5% missing data is accepted) [40, 41].In case of multicollinearity between (ICC > 0.70) between prognostic variables one will be excluded;If a variable lacks agreement (ICC ≤0.70) with CAI it will be excluded;In case the prevalence of CAI during the study differs from the estimated 30%. In case the percentage of patients progressing to CAI exceeds the 50%, the sample size calculation will be based on the number of non-events. The prevalence will be recalculated when 500, 750, 1000, 1250, 1500, 1750,2000 and 2250 patients have returned the last questionnaire to minimize patient burden, as inclusion will stop as soon as the minimal required sample size is reached.

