## Discussion

Currently patients with CAI suffer for an unnecessary long period of time as they are unaware of treatment option and often are not eligible for direct surgical stabilization. By developing a risk assessment model tested for its validity, patients at risk may be identified and receive appropriate treatment. The current model is the first to address the progression to CAI on a large scale including both internal and external validation. Focusing on bone geometry, sex and height means focusing on factors patients cannot control despite their potential role in progressing to chronicity [8]. As patients will want to return to their old level of sports, the additional inclusion of sports intensity reflects the risk of exposure to loading events that cause recurrent sprains. BMI and height, despite their strong correlation, are included as they both have been extensively described as a prognostic factor and should be included. However, as the inclusion of both factors will create bias, the factor with the strongest correlation with CAI will be included in the model.

In case of CAI, patients become eligible for surgical stabilization after 6 months of failed conservative treatment [4, 5]. Normally after an ankle sprain, it is assumed that the complaints will automatically resolve, and physicians lose track of the patients and thus do not have a proper follow-up. Patients that progress to CAI, unaware of treatment options, often experience complaints for unnecessary long period of time.

With a risk assessment model that has the potential to identify patients at risk for CAI, patients can be properly informed on treatment options prior to becoming chronic. Patients pre-identified as being at risk, may receive adequate follow-up [42]. Additionally knowing about the potential course of complaints and treatment options, patients that still experience complaints after 6 months, and therefore progressed to chronic instability, can ensure they are seen by a physician on time. This way they can become eligible for relatively early surgical stabilization, not experiencing complaints for an unnecessary long period of time, in turn increasing the success rate of surgery [7].

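### Excluding patients for any surgery up to month 12 removes CAI cases operated on between months 6 and 12, so observed prevalence and average predicted risk come out too low

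*Protocol article*

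**What the plan says.** The exclusion column of Table 1 (Study centres and participants) lists "Acute surgical repair or the ATFL/CFL or any other form of surgery within 12 months after the ER visit". The second half of that criterion covers the whole outcome window and can be checked only after the ER visit.

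The outcome is fixed at 12 months. Definition CAI requires giving way, recurrent sprains, a sensation of instability and disability "that has not resolved in the time-frame from the first initial sprain up to the 12-months follow-up". Study design makes only the 12-month questionnaire mandatory for the diagnosis.

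Surgery becomes available halfway through that window. Follow-up states: "In case of persisting complaints six months after the ER visit, patients will be eligible for surgical treatment according to Dutch standards". The Discussion links this to the outcome: "In case of CAI, patients become eligible for surgical stabilization after 6 months of failed conservative treatment". It also refers to "patients that still experience complaints after 6 months, and therefore progressed to chronic instability, can ensure they are seen by a physician on time".

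The article does not count an operated patient as a CAI case, does not treat surgery as an intercurrent or competing event, and plans no sensitivity analysis for it. Prognostic model (Data analysis and statistics) uses a temporal split of the same cohort for external validation. It aims at cut-offs that point to surgery, watchful waiting or no surgery.

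**The concern.** A prediction model should be developed in the patients to whom it will be applied. Here that means patients seen at the ER, when nobody knows who will be operated on later. The exclusion depends on a later event, and that event is made likelier by developing the outcome. Patients who recover have no comparable route to surgery for instability. Deletion therefore falls on cases rather than non-cases.

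The quantity at stake is absolute risk. The model is meant to yield cut-offs that inform a surgical decision, so a downward shift in predicted risk moves patients across those cut-offs. The planned safeguards do not catch it. The temporal validation set has had the same patients removed, so the model would look calibrated there. The prevalence re-checks in PREDICT sample size would adjust the required number to the depleted prevalence but would not correct the prevalence itself.

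**Working it through.** **The plan's own figures.** Inputs from Table 2 and PREDICT sample size: 20 events per variable, 16 coefficients, prevalence 30–40%, 10% loss to follow-up.

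- Events needed: 20 × 16 = 320.
- At 30%: 320 / 0.30 / 0.90 = 1185.2 (stated: 1185).
- At 40%: 320 / 0.40 / 0.90 = 888.9 (stated: 889).
- Two sets: 2 × 1185 = 2370 (stated: 2370).

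The sample size reproduces. The 10% allowance is labelled loss to follow-up, and nothing is added for surgical exclusions.

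**Effect of the exclusion.** Let p be the true proportion with CAI and s the share of those cases operated on, and so excluded, before month 12. The article does not give s, so the values below are assumptions.

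- Observed prevalence = p(1 − s) / (1 − ps). Example: 0.30 × 0.90 / (1 − 0.03) = 0.27 / 0.97 = 27.8%.
- If surgery depends only on being a case, each retained patient's odds of CAI are multiplied by (1 − s). The logistic intercept then shifts by ln(1 − s) and the slopes stay the same. A true risk r is predicted as r(1 − s) / (1 − rs).
- Events left among 1185 enrolled at 30%: 1185 × 0.90 × 0.30 × (1 − s).

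| Share of cases operated on, s | Observed prevalence, true 30% | Observed prevalence, true 40% | Intercept shift | True 60% risk predicted as | Events (per variable) |
|---|---|---|---|---|---|
| 2% | 29.6% | 39.5% | −0.02 | 59.5% | 314 (19.6) |
| 5% | 28.9% | 38.8% | −0.05 | 58.8% | 304 (19) |
| 10% | 27.8% | 37.5% | −0.11 | 57.4% | 288 (18) |
| 20% | 25.5% | 34.8% | −0.22 | 54.5% | 256 (16) |
| 30% | 23.1% | 31.8% | −0.36 | 51.2% | 224 (14) |

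**Direction.** The table assumes that every excluded patient would have been a case at month 12. More generally, let a fraction o of the cohort be operated on, of whom a proportion g would have had CAI. Observed prevalence is then (p − og) / (1 − o), which is below p whenever g exceeds p. Patients operated on because complaints persisted should satisfy this easily.

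**Coefficients.** A simulation used 400,000 patients, one normal predictor, a true slope of 0.80 and a true prevalence of 30.2%:

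| Who is operated on | Cases removed | Fitted slope | Mean predicted risk, full cohort |
|---|---|---|---|
| Depends on case status only | 20.1% | 0.79 | 26.2% |
| More often at high predictor values | 25.2% | 0.63 | 25.4% |
| More often at low predictor values | 19.3% | 0.96 | 25.8% |

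Average predicted risk falls in all three scenarios. The slope can stay the same, shrink or grow.

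**The case against.** The strongest objection is about size. Only patients actually operated on by month 12 are lost; those who are eligible but not operated on stay in and count as CAI. The article's own account points to limited early surgery. The Discussion says physicians lose sight of these patients, who are often unaware of their options, and Follow-up says a large proportion recover conservatively. At 2–5% uptake, prevalence moves only to 29.6–28.9%, which is small beside the plan's 30–40% range. This stands: the effect may be small. It does not remove the contradiction, and the article gives no figure that would bound it.

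A second defence is that the target is risk under conservative treatment. That supports excluding acute repair given as initial treatment. It does not justify deleting later operations. Deletion is harmless only if the operated patients would have had CAI as often as others with the same predictors, and they were selected because complaints persisted.

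Third, counting surgery as an event brings a treatment decision into the outcome and departs from the literal definition. If more active patients seek surgery, sports intensity could be linked to the outcome partly through that choice. This is a fair cost, and the sensitivity analyses are there to show it.

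A reader might also infer three stronger claims, which the article does not support:

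- *Coefficients are attenuated.* This is one scenario of the three above.
- *Events per variable fall for good.* The planned prevalence re-checks can restore them by recruiting more patients, so the cost is recruitment rather than precision.
- *The exclusion "A diagnosed OCD after primary inclusion" biases the model in the same way.* That needs later imaging to be commoner in patients who do not recover, which the article does not say. Leaving out a different joint lesion is a defensible choice.

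**Conclusion.** The point holds for absolute risk. Table 1 and the statements on surgery from six months conflict, and as written the plan deletes CAI cases because of a post-baseline consequence of the outcome. Observed prevalence and average predicted risk are biased downward whenever patients operated on for instability would have had CAI more often than the rest of the cohort. The planned temporal validation cannot detect this.

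The magnitude is unknown because the operated share is not given. Over an assumed 2–30% of cases, a true 30% prevalence appears as 29.6–23.1%, and a true individual risk of 60% as 59.5–51.2% if surgery depends only on case status. It would be too strong to say that everyone eligible at six months is removed, or that predictor effects are generally weakened.

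**What to change.** Reconcile Table 1 with Follow-up and the Discussion, as a matter of analysis population only:

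- Limit the surgical exclusion in the analysis to acute ligament repair as initial treatment.
- Keep patients later operated on for persistent ankle instability and count them as CAI events in the primary analysis.
- Classify patients operated on for other reasons by their last pre-operative or their 12-month questionnaire status, under a rule stated in advance.
- Report the number operated on, with timing and reason.
- Add two sensitivity analyses: (i) operated patients classified by last pre-operative questionnaire status; (ii) the present exclusion.
- Leave the exclusion for an OCD diagnosed after inclusion in the primary analysis; at most, add a sensitivity analysis that retains those patients.

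The cost is an amendment to Table 1, a record of the date and reason for surgery (the questionnaires already ask about treatment), and two extra analyses. The downside is small: a few operated patients might have recovered by month 12, and a treatment decision enters the outcome. Comparing the primary result with the two sensitivity analyses shows how much either matters. If operated cases count as events, the planned 320 events from 1185 patients at 30% prevalence hold again. Nothing here bears on who should be operated on or when.

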### Definition CAI

Chronic ankle instability is defined as: *The perception of ‘giving-way’, in combination with a history of recurrent ankle sprains, the sensation of ankle instability and persistent disabilisty (pain, swelling* etc.*) that has not resolved in the time-frame from the first initial sprain up to the 12-months follow-up* [3, 25, 26]*.*

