## Background

Chronic ankle instability (CAI) is a worldwide common sports orthopaedic problem. It mainly results from a lateral ankle sprain, progressing in up to 30–40% of patients to CAI despite adequate initial treatment [1, 2]. It is mainly defined as persisting complaints of giving way, pain and recurrent ankle sprains for at least 12 months [3]. Patients with CAI are generally eligible for surgery, whereas in the Netherlands in case of acute ankle instability mainly only professional athletes qualify for surgical stabilization [4, 5].

Repeatedly spraining the ankle, as occurs in patients with CAI, can have serious consequences such as damage to the ankle joint and osteoarthritis on the long term [6]. When early surgical treatment is performed, it leads to better results compared to late surgical repair after both ruptures and ligament laxity [7]. However, currently it cannot be adequately assessed which patients will not respond to conservative treatment and will develop CAI directly after an ankle sprain.

To determine who is eligible for early surgical treatment the contributing risk of prognostic factors should be determined. Many prognostic and risk factors for ankle sprains and ankle instability have been studied. Kobayashi et al. [8] wrote a critical review in 2014 outlining the many neuromuscular factors that have been studied and whether they are correlated to ankle instability. They concluded it was difficult to compare the findings as there was a lack of standardization for inclusion. Other factors that have been studied on their potential contribution to ankle instability are factors such as patient characteristics [9, 10], foot and ankle configuration [11–15], joint pathology [16–18] and treatment [19–23].

A large amount of factors associated with ankle sprains are of neuromuscular origin. An adequate rehabilitation program may help prevent progression to chronicity [8]. Other factors, for example patient characteristics, foot and ankle configuration and joint pathology, are already present at time of the initial sprain. These factors will not be positively influenced by a functional training program in contrast to neuromuscular associated factors. A risk assessment model based on factors that cannot be changed by rehabilitation programs, using standardized inclusion criteria, may therefore provide a reliable risk analysis on the development of chronic complaints.

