**Fig. 6 Fig6:**
[figure not shown]
The Talar Convexity Angle (TCA) is formed by connecting the posterior talar tubercle (**a**), the most proximal part of the talus (**b**), and the deepest point of the transition to the talar neck (**c**)

Secondly, (12) age, (13) sex, (14) height, (15) BMI and (16) sports intensity (by means of the Ankle Activity Index (AAI)) will be implemented in the model as important patient characteristics, in case of a significant correlation. All these variables have shown a (prospective or retrospective) correlation with ankle instability in previous research apart from MDTA, MMHA and TCA. These three, however, have shown a relation with other pathologies that also concern an inversion-plantarflexion trauma mechanism and will therefore be explored on a potential correlation with CAI [14, 16, 30].

To assess overall recovery and CAI at 12 months, a questionnaire including patient reported outcome measures (PROMs) will be used. This questionnaire includes the FAOS and CAIT. The FAOS is a Dutch validated questionnaire assessing pain, other symptoms (swelling, locking, mobility, stiffness), function (activities of daily living) and sports and foot- and ankle related quality of life divided over 5 subscales, with scores ranging from 0 to 100 [31, 32]. The CAIT is scale consisting of 9-items measuring the severity of functional ankle instability per ankle individually. The total score ranges from 0 to 30 with a cut-off value discriminating between a functionally stable and instable ankle of 11.5 points (as calculated for the Dutch population) [33, 34].

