### Missing data

A per protocol analysis is applied based on patients filling out at least one questionnaire and having an available AP and lateral radiograph for radiographic assessment. In case the last questionnaire is missing, on which the diagnosis of CAI will be based, and the question concerning persisting complaints at six or twelve months is not answered, differentiation between full recovery or progression to chronicity cannot be made. For this reason these patients and patients with a missing radiograph will be excluded.

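### CAI at 12 months, the outcome of the model, is not assigned by one rule: the missing-data fallback, one-year contact and questionnaire are not tied to the stated definition

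*Protocol article*

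**What the plan says.** **Definition CAI** gives the formal definition: giving-way "in combination with a history of recurrent ankle sprains, the sensation of ankle instability and persistent disabilisty", not resolved between the first sprain and the 12-month follow-up. All the listed components are joined.

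**Study design** makes only the 12-month questionnaire mandatory for diagnosing CAI. **Table 1** requires one of the earlier questionnaires plus the 12-month follow-up.

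**Missing data** calls the last questionnaire the basis of the diagnosis. It then says that if this questionnaire is missing and "the question concerning persisting complaints at six or twelve months is not answered, differentiation between full recovery or progression to chronicity cannot be made". Those patients are excluded.

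**Follow-up** adds a further contact so that no CAI case is missed: "one year after their ER visit they will be contacted, inquiring on persisting complaints and ankle instability". The same section takes patients who report sprains before the ER visit out of the primary analysis.

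**Clinical outcome measures** (text after Fig. 6) states: "To assess overall recovery and CAI at 12 months, a questionnaire including patient reported outcome measures (PROMs) will be used". It names the FAOS and CAIT and reports for the CAIT a "cut-off value discriminating between a functionally stable and instable ankle of 11.5 points". Follow-up describes the purpose of these instruments differently: "the Cumberland Ankle Instability Tool (CAIT) to evaluate recovery".

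**The concern.** Every later step uses one yes/no variable: the screening of candidate predictors, the logistic model, the ROC-based cut-offs meant to inform advice on surgery, and the prevalence checks that reset the sample size. If some patients are labelled by the full conjunction and others by one answer about complaints, that variable means different things in different rows. The difference would follow response behaviour, because only patients without the last questionnaire fall under the fallback.

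The recurrent-sprain component raises a second question. Whether it is required in a first-sprain cohort affects which predictors look prognostic, above all sports intensity.

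**Working it through.** **1. The sections side by side**

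| Section | What it uses | Recurrent sprain needed? | Time point |
|---|---|---|---|
| Definition CAI | giving-way, recurrent sprains, felt instability and lasting disability together | yes | up to 12 months |
| Study design, Table 1 | 12-month questionnaire or follow-up, mandatory | not stated | 12 months |
| Missing data (last questionnaire absent) | one question on persisting complaints | no | six or twelve months |
| Follow-up, one-year contact | complaints and instability | not mentioned | 12 months |
| Clinical outcome measures | questionnaire including FAOS and CAIT | not stated | 12 months |

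No section maps the questionnaire items, the contact or the complaints question onto the definition, or ranks them.

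**2. Three patients**

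- *Last questionnaire missing; complaints reported at six months.* Missing data does not exclude this patient and lets the answer stand for progression to chronicity. Definition CAI cannot be applied, because the state at 12 months and the other components are unknown. Study design and Table 1 would leave the patient out.
- *Same patient, but the complaints resolve by month 12.* The fallback label is still chronic. Under Definition CAI the patient is not a case.
- *12-month questionnaire complete; giving-way, felt instability and pain, but no new sprain.* Read literally, Definition CAI makes this a non-event. No other section gives a rule that makes it an event, but none confirms that a re-sprain is required.

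**3. The recurrent-sprain component**

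Patients with earlier sprains are outside the primary analysis. Everyone analysed therefore starts with the index sprain only, and recurrence can come only from a new sprain in the follow-up year. The Discussion says that sports intensity reflects exposure to events that cause recurrent sprains, and sports intensity is candidate predictor 16. If a re-sprain is required, part of that predictor's association comes through the outcome definition. If it is not required, that part falls away. Either choice can be defended, but it has to be made in advance.

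**4. Link to the sample size**

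Inputs (PREDICT sample size, Table 2): 20 events per variable, 16 variables, 30–40% prevalence, 10% loss.

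- Events: 20 × 16 = 320.
- N at 30%: 320 / 0.30 / 0.90 = 1185.2, against 1185 stated. Two cohorts: 2 × 1185 = 2370, as stated.
- N at 40%: 320 / 0.40 / 0.90 = 888.9, against 889 stated.

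The arithmetic reproduces. The prevalence depends on the event rule, and the document gives none by rule. Purely as assumed values, with 1185 × 0.90 = 1066.5 evaluable patients:

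- 15%: 1066.5 × 0.15 / 16 = 10.0 events per variable
- 20%: 13.3
- 30%: 20.0
- 40%: 26.7

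This shows sensitivity to prevalence. It does not estimate what either rule would yield.

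**The case against.** The strongest reply is that the Methods contain one headed definition and that the other sections describe data sources. Much of this stands, and it rules out several stronger readings:

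- **That a CAIT score below 11.5 decides CAI.** The text reports 11.5 as the instrument's threshold for a functionally stable ankle and never makes it a case rule. Follow-up assigns the CAIT to recovery.
- **That a patient with complete 12-month data is an event under one section and a non-event under another.** The complaints question appears only where the last questionnaire is missing. For completers, Missing data points to that questionnaire.
- **That the one-year contact applies a looser rule.** It is described as case-finding and no classification rule is given. Its description omits recurrent sprains, which leaves a gap but does not prove a second definition.
- **That six months of complaints is the endpoint.** The Discussion does speak of "patients that still experience complaints after 6 months, and therefore progressed to chronic instability", but in prose about timely access to care.
- **That the study will fall short of events.** The 30–40% figure stands in the Background beside a description of CAI as "persisting complaints of giving way, pain and recurrent ankle sprains for at least 12 months", which includes recurrence, so nothing shows that it belongs to a complaints-only rule. PREDICT sample size also provides for recalculation if prevalence differs.

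An article may also leave item wording to the full protocol. That does not answer the fallback, which is stated here and conflicts with the definition and the mandatory 12-month assessment stated here. Recalculation does not answer it either: it adjusts the number of patients but takes over whichever event rule produced the prevalence.

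**Conclusion.** The point holds in limited form. The firm contradiction lies between Missing data on one side and Definition CAI, Study design and Table 1 on the other. Following the fallback would put outcomes defined by a single answer, possibly from six months, into the same model as outcomes defined by the conjunction at 12 months. This rests on reading the exclusion as needing both conditions, a missing last questionnaire and an unanswered complaints question, which is what the sentence says.

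The one-year contact, the PROM questionnaire and the re-sprain requirement are unreconciled ambiguities and not contradictions.

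The number of patients affected, and any shift in prevalence or coefficients, cannot be derived from the document. The planned sample size is arithmetically sound for a 30% prevalence; what is open is which event rule that prevalence describes.

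**What to change.** - Reconcile Definition CAI, Study design, Table 1, Follow-up, Clinical outcome measures and Missing data into one event rule, applied identically to the 12-month questionnaire and the one-year contact. Both must then collect every component of the rule.
- State whether a sprain after the index sprain is required.
- Remove the persisting-complaints question, and in particular the six-month answer, as a stand-alone classifier. Treat patients with nothing more than that as missing the outcome.
- Confirm that the 30–40% prevalence behind the sample size refers to the chosen rule, and use the same rule at each planned prevalence check.
- Optionally, refit the model with CAIT below 11.5 on the index ankle as a named sensitivity outcome.

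The cost is protocol wording and, where components are not yet asked, a few items in the questionnaire and contact script. The downside is slightly more patients with a missing outcome and possibly a restated prevalence, which the existing recalculation provision can absorb. The rule should be fixed before outcomes are analysed, so that it cannot be chosen in the light of the results.
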